## Abstract

**Background:**

Patient safety performance can be assessed with several systems, including passive and active surveillance. Passive surveillance systems provide opportunity for health care personnel to confidentially and voluntarily report incidents, including adverse events, occurring in their work environment. Active surveillance systems systematically monitor patient encounters to seek detailed information about adverse events that occur in work environments; unlike passive surveillance, active surveillance allows for collection of both numerator (number of adverse events) and denominator (number of patients seen) data.

Chiropractic manual therapy is commonly used in both adults and children, yet few studies have been done to evaluate the safety of chiropractic manual therapy for children. In an attempt to evaluate this, this study will compare adverse event reporting in passive versus active surveillance systems after chiropractic manual therapy in the pediatric population.

**Methods/design:**

This cluster randomized controlled trial aims to enroll 70 physicians of chiropractic (unit of randomization) to either passive or active surveillance system to report adverse events that occur after treatment for 60 consecutive pediatric (13 years of age and younger) patient visits (unit of analysis). A modified enrollment process with a two-phase consent procedure will be implemented to maintain provider blinding and minimize dropouts. The first phase of consent is for the provider to confirm their interest in a trial investigating the safety of chiropractic manual therapy. The second phase ensures that they understand the specific requirements for the group to which they were randomized.

Percentages, incidence estimates, and 95% confidence intervals will be used to describe the count of reported adverse events in each group. The primary outcome will be the number and quality of the adverse event reports in the active versus the passive surveillance group. With 80% power and 5% one-sided significance level, the sample size was calculated to be 35 providers in each group, which includes an 11% lost to follow-up of chiropractors and 20% of patient visits.

**Discussion:**

This study will be the first direct comparison of adverse event reporting using passive versus active surveillance. It is also the largest prospective evaluation of adverse events reported after chiropractic manual therapy in children, identified as a major gap in the academic literature.

**Trial registration:**

ClinicalTrials.gov, ID: NCT02268331. Registered on 10 October 2014.

**Electronic supplementary material:**

The online version of this article (doi:10.1186/s13063-017-2301-0) contains supplementary material, which is available to authorized users.

## Background

### Pediatric chiropractic manual therapy and patient safety

Chiropractic manual therapy usually involves the therapeutic application of a force to a pre-determined body structure, which is typically a vertebral or extremity joint. There are numerous manual therapy variations with the velocity, amplitude, loading frequency, choice of lever, location, direction of load, and treatment frequency changing widely amongst the variations [1]. Spinal manipulation therapy (SMT), a type of manual therapy, is regulated for use in many professions (e.g., doctor of osteopathy, medical physicians, and physical therapists), but doctors of chiropractic (DCs) are the most likely to use SMT on a regular basis [2]. According to a 2015 practice analysis of United States DCs, 17.1% of chiropractic patients are 17 years of age or less; this increases to 38.7% amongst DCs who specialize in pediatrics [2, 3].

Adverse events after manual therapy, including SMT, have been investigated more thoroughly in adult patients than in children [4–7]. Several reviews of adverse events in children following manual therapy have identified rare serious adverse events, although the studies have been primarily case reports. The main conclusion from these reviews was that there is insufficient primary research on this topic in this population [8–10].

### Patient safety performance – surveillance systems

To measure safety performance, including reporting of adverse events, many health care settings have implemented surveillance systems to report and learn from adverse events. When established, such systems can provide learning opportunities based on the information gathered [11].

These patient safety surveillance systems vary according to their purpose. *Active surveillance* systematically collects information from the provider about patient encounters, including adverse events, which enhances reporting and demonstrates a health care organization’s commitment to patient safety [11]. Although active surveillance can generate higher quality and quantity of reports because both numerator and denominator data are known, the time and resources needed to properly execute an active surveillance reporting system are often limitations to its successful implementation.

*Passive surveillance* voluntarily collects adverse event information from the provider and is more commonly utilized throughout health care [12]. Typically, passive surveillance systems are conducted confidentially and sometimes anonymously, and some have been modified for Internet-based fora. These systems can also promote quality improvement by allowing for reporting of adverse events, near misses (an event that could have caused an adverse event, but did not), and unsafe conditions. Passive surveillance systems are relatively easy to implement and can collect reports from a broad range of topics and individuals [12]. However, their major limitations include under-reporting (quantity of reports), inadequate information (quality of reports), and limited knowledge of how many patients were exposed (denominator data). Practitioners involved with passive surveillance systems have reported that they commonly forget to write-up their report, are too busy to review others’ reports, are not sure who is responsible to write-up a report, or do not report an event because it seemed trivial [13].

### Study justification

Within the chiropractic profession, active surveillance reporting systems are not used routinely. A passive surveillance system for chiropractic care, called the “Chiropractic Patient Incident Reporting and Learning System” (CPiRLS), is currently being used in Europe and Australia [14, 15]. Although CPiRLS does not have any age restrictions, to date only limited pediatric data have been reported into the system, despite multiple calls for high-quality safety data about pediatric chiropractic manual therapy [8, 10].

Both active and passive surveillance methods have distinct advantages and limitations. The need for a direct comparison of the ability of active versus passive surveillance to report adverse events, and the need to better understand the patient safety performance in the use of chiropractic manual therapies for the pediatric population, led to the development of this cluster randomized clinical trial.

### Study aim and hypothesis

Study aim: to compare the quantity and qualify adverse event reports after chiropractic manual therapy in children 13 years of age or under, using passive versus active surveillance reporting systems. *Hypothesis: DCs randomized to the active surveillance system will report more adverse events and will have better quality reporting than those randomized to the passive surveillance system.*

## Methods

### Study design

The study design is a pragmatic, superiority, cluster randomized clinical trial with a modified enrollment process to maintain participant blinding. DCs in private practice who treat children will be the unit of randomization with random allocation in a 1:1 ratio to active or passive surveillance reporting systems. Cluster randomization was chosen for practical reasons with the unit of analysis being reports from the individual chiropractic patient visits. The University of Alberta’s Research Ethics Board reviewed and approved this study (Pro00027903). The trial has been registered at ClinicalTrials.gov (NCT02268331). The study protocol was prepared using the Standard Protocol Items: Recommendations for Interventional Trials (SPIRIT) guidelines [16] (see Additional file 1) and also the “Methods” section of the Consolidated Standards of Reporting Trials (CONSORT) 2010 Checklist for reporting a cluster randomized controlled trial [17] (see Additional file 2).

### Recruitment, randomization, and enrollment

Licensed DCs in the United States and Canada will be recruited from a variety of venues, including pediatric chiropractic-specific events and organizations, social media, and professional newsletters/magazines. Word of mouth and referrals from colleagues and past participants will also be source of referral into the study.

As shown in Fig. 1, DCs interested in the study will complete a demographic questionnaire and review/sign the initial consent document, which states that they are interested in enrolling in a study to report safety information from 60 consecutive pediatric visits. They will then be randomized to passive or active surveillance by the study coordinator ([name]). To promote baseline equivalence, we will stratify by DC’s self-reported average proportion of pediatric patients seen (>20% versus ≤ 20%). To maintain allocation concealment, the REDCap (Research Electronic Data Capture) Randomization Module will be utilized with a random, variable, permuted block size, generated by an independent biostatistician [18]. Interested DCs will have study materials sent directly to their offices. This material includes the Consent Form that gives details on the surveillance system to which they were randomly assigned. DCs are considered enrolled in the study after that Consent Form is signed and they complete the online baseline survey, which collects additional demographic data and assesses patient safety attitudes [19]. Throughout study participation, to ensure compliance with study methods, regular communications will occur via email or telephone between the study coordinator ([name]) and the DC.

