### Outcomes

The primary outcome will be the number (the count) and quality (i.e., ability to meaningfully interpret/adjudicate, a binary variable) of the DC’s adverse event(s) reports per patient visit and per patient in each group. Quality of adverse event reports will be assessed by the adjudicators’ ability to meaningfully adjudicate the report (section above).

A secondary outcome is the change in patient safety attitudes for participating DCs. This will be measured in both groups using the Safety Organizing Scale [19], which is a nine-item survey with a 7-point rating scale (1 – “Not at all”; 7 – “To a very great extent”). This questionnaire is to be completed at two time points: at baseline (the online baseline survey prior to study enrollment) and after adverse event data collection is complete for each participating DC. In the active surveillance arm, additional variables to assess adverse events and associated factors for adverse events include: patient-reported adverse events, manual therapy treatment description, patient health history, and patient satisfaction [22].

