### Statistical methods

The count of reported adverse events (any severity) in each group will be expressed with percentages and incidence estimates, and their 95% confidence intervals (CIs). The primary analysis will compare the cumulative incidence of adverse event reports in active versus passive surveillance. Because the outcome is number of events, it is assumed that the data will follow a Poisson distribution. Hence, a Poisson regression with log links will be used in general estimating equation (GEE) analyses with an appropriate sandwich estimator to take into account the DC cluster correlation. Groups will be compared using an intention-to-treat analysis.

Sensitivity analysis, using the same GEE analyses as above, will be conducted for reports that were not adjudicated (because of uninterpretable adverse events) and differences in how missing data were handled (i.e., imputing using average incidence and highest incidence). The binary variable expressing if the quality of the adverse event report allowed for meaningful interpretation/adjudication will be evaluated using the McNemar’s exact test because of the expected rarity of reports and cluster correlation.

Secondary analysis will address differences in the count of adverse event reports by patient-only, provider-only, and those reported by the active surveillance versus the provider-reports in the passive surveillance. Like the primary analyses, Poisson regression with log links will be used in GEE analyses to account for cluster-specific methods. Patient safety attitudes will be measured before and after participation and compared across surveillance groups.

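### The baseline safety-attitude survey is completed after randomisation and after doctors of chiropractic have been sent their own arm's materials, so the starting value of this secondary outcome may already carry some effect of allocation

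*Protocol article*

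**What the plan says.** The section on recruitment, randomization and enrollment in the protocol article sets out the sequence. First, "DCs interested in the study will complete a demographic questionnaire and review/sign the initial consent document". Next, "They will then be randomized to passive or active surveillance by the study coordinator". Study materials then go to the DC's office: "This material includes the Consent Form that gives details on the surveillance system to which they were randomly assigned". Finally, "DCs are considered enrolled in the study after that Consent Form is signed and they complete the online baseline survey". That survey is the one "which collects additional demographic data and assesses patient safety attitudes".

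The Outcomes section makes the survey the first of two measurements: "A secondary outcome is the change in patient safety attitudes for participating DCs", taken with the nine-item Safety Organizing Scale "at baseline (the online baseline survey prior to study enrollment) and after adverse event data collection is complete". The Statistical methods section adds: "Patient safety attitudes will be measured before and after participation and compared across surveillance groups". It names no model for that comparison.

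**The concern.** A baseline protects a between-arm comparison of change because allocation cannot have influenced it. Here the DC has been randomised and sent a description of the assigned system before rating safety attitudes. In one arm that system involves forms around each of 60 visits; in the other it involves incident reporting guided by a trigger list. Reading about a safety system could shift answers about safety, and the shift could differ between arms.

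If the shift runs in the same direction as the eventual effect, part of that effect is subtracted out of the reported change. If it runs the other way, the change is exaggerated. In addition, DCs who decline once they see their arm supply no baseline score, so the trial cannot show whether they differ from those who stayed. The article itself expects the active arm to be the more demanding one.

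**Working it through.** **Order of events.** The claim concerns sequence, so the check is to line up the steps.

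| Step | What happens | Relative to randomisation |
|---|---|---|
| 1 | Demographic questionnaire and first consent, which does not describe the arms; no attitude scale is mentioned | Before |
| 2 | Randomisation | – |
| 3 | Materials with the arm-specific consent form are sent | After |
| 4 | Second consent signed and online survey with the attitude scale completed; the DC then counts as enrolled | After |
| 5 | Data collection, then the second attitude survey | After |

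The Outcomes section places the first survey before enrolment. That does not place it before randomisation, because enrolment is defined at step 4 and requires the survey itself. The section on minimization of systematic error agrees: the second consent follows randomisation and explains the procedures of the DC's own group.

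**Size.** The article gives no standard deviation, expected effect or power for the Safety Organizing Scale, so no bias can be computed from it. An illustration needs assumptions. Let Δ be the between-arm effect on the end-of-study score, f the fraction of Δ already present in the late baseline, and b the within-arm slope of end score on baseline.

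- Change-score contrast: Δ − fΔ = (1 − f)Δ
- Baseline-adjusted contrast: Δ − b·fΔ = (1 − fb)Δ
- End score alone: Δ, because f does not enter

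| f (assumed) | Change score keeps | Adjusted, b = 0.3 | Adjusted, b = 0.7 |
|---|---|---|---|
| 0.10 | 90% | 97% | 93% |
| 0.25 | 75% | 92.5% | 82.5% |
| 0.50 | 50% | 85% | 65% |

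For example, with f = 0.25 and b = 0.7: 1 − 0.25 × 0.7 = 0.825.

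**Sample size.** The only design figure in the article is 35 DCs per arm, for the primary outcome. It reproduces. A one-sided 5% test of 4.3% against 0.53% at 80% power needs 204 independent visits per arm. With 60 × 0.8 = 48 evaluable visits per DC, the design effect is 1 + 47 × 0.13 = 7.11. Then 204 × 7.11 / 48 = 30.2, rounded up to 31, and 31 / 0.89 = 34.8, rounded up to 35. The survey date plays no part in it.

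**The case against.** The best defence is that the survey still precedes any use of either system. If the question is how attitudes change while a DC operates a surveillance system, only the reading of a consent form and related materials can contaminate the baseline. The two-phase consent also conceals the comparison and the other arm, so the DC has no contrast to react to. Both points stand as reasons to expect a modest effect. Neither makes the value a pre-allocation one, since the DC's own procedures are disclosed.

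A reader might infer more than the article supports:

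- **That every DC has signed the second consent before answering.** Signature and survey are two conditions for enrolment. Their order is suggested by the sentence but not stated as a rule, and the flow chart is not shown. What is clear is that the survey follows randomisation and the sending of materials.
- **That a baseline shift biases the result one for one.** That holds for a change-score contrast only, and the article names no model. The choice of model for precision is a separate matter from timing.
- **That the late survey causes arm-specific refusal.** Refusal after allocation comes from the two-stage consent. The survey date only determines whether decliners can be described.
- **That the additional demographics in the survey are spoiled.** Reading a consent form does not alter fixed characteristics. They are exposed only to selection, and a demographic questionnaire and the stratification variable are already collected before randomisation.

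**Conclusion.** The point holds in a limited form. The starting value for change in safety attitudes is post-allocation: it follows randomisation and the dispatch of arm-specific materials, and probably the second signature. It may contain some effect of learning one's own arm, and it exists only for DCs who accepted that arm. Nothing in the article shows that allocation has in fact moved the scores. The size of any shift is unknown, and the percentages above rest wholly on assumed values of f and b. One secondary outcome is affected. It would be wrong to conclude that the primary comparison of adverse event reports or the 35 DCs per arm is undermined. The change is worth making because it is cheap and removes an avoidable doubt.

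**What to change.** For DCs not yet randomised, collect the Safety Organizing Scale with the demographic questionnaire at the first-consent step, before the REDCap randomisation. The contact already exists, and a nine-item scale there reveals nothing about the arms. In the Outcomes section, define the baseline by reference to randomisation rather than enrolment.

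For DCs already surveyed after allocation, record that timing with a flag. Add a sensitivity analysis that compares end-of-study scores between arms without adjusting for the post-allocation baseline, and state the limitation in the report.

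The cost is the reordering of part of one survey, a minor ethics notification, and a few surveys from DCs who later decline. The article reports active recruitment at submission, so the trial of 70 DCs would also contain two baseline timings, which the flag makes visible. The earlier survey would describe DCs who decline after allocation. It would not remove arm-specific refusal, and those DCs would still lack an end-of-study score.

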**Fig. 1 Fig1:**
[figure not shown]
Flow chart of study activities

Causality (i.e., relatedness)	*Certain*: a clinical event occurring in a plausible time relationship to treatment, and which cannot be explained by concurrent disease or other drugs or therapies
	*Probable/likely:* a clinical event with a reasonable time sequence to treatment, unlikely to be attributed to concurrent disease or other drugs or therapies
	*Possible:* a clinical event with a reasonable time sequence to treatment, but which could also be explained by concurrent disease or other drugs or therapies
	*Unlikely:* a clinical event with a temporal relationship to treatment which makes a causal relationship improbable, and in which drugs, other therapies or underlying disease provide plausible explanations
Preventability	1: Virtually no evidence of preventability
	2: Slight to modest evidence of preventability
	3: Preventability not quite likely (less than 50/50, but “close call”)
	4: Preventability more than likely (more than 50/50, but “close call”)
	5: Strong evidence of preventability
	6: Virtually certain evidence of preventability
Patient disposition	1: Resolved, no sequelae
	2: AE still present – no treatment
	3: AE still present – being treated
	4: Residual effects present – no treatment
	5: Residual effects present – treated
	6: Death
	7: Unknown

### Comparison arm: passive surveillance

The passive surveillance system will use the established *Chiropractic Patient Incident Reporting and Learning System* (CPiRLS) [15]. DCs will be asked to report adverse events that occur in 60 consecutive pediatric patient visits. In this system, only registered providers can submit, read or comment on reports. Participating DCs will be given a universal code to protect anonymity and will also be provided with the CPiRLS’s “trigger list” to advise on what kinds of incidents/adverse events should be reported (see Additional file 4). Reports and comments submitted will be monitored by both the CPiRLS team and the study’s investigators.

### Adjudication

In both the active and the passive groups, when a moderate, severe or serious adverse event is identified, all information from the report will be reviewed independently by blinded content experts to evaluate the event according to the terminology outlined in Table 1 (causality, preventability, and patient disposition). Operational definitions for all terminology were determined through a consensus-based process by the SafetyNET team of manual therapy and patient safety experts [20, 21].

### Outcomes

The primary outcome will be the number (the count) and quality (i.e., ability to meaningfully interpret/adjudicate, a binary variable) of the DC’s adverse event(s) reports per patient visit and per patient in each group. Quality of adverse event reports will be assessed by the adjudicators’ ability to meaningfully adjudicate the report (section above).

A secondary outcome is the change in patient safety attitudes for participating DCs. This will be measured in both groups using the Safety Organizing Scale [19], which is a nine-item survey with a 7-point rating scale (1 – “Not at all”; 7 – “To a very great extent”). This questionnaire is to be completed at two time points: at baseline (the online baseline survey prior to study enrollment) and after adverse event data collection is complete for each participating DC. In the active surveillance arm, additional variables to assess adverse events and associated factors for adverse events include: patient-reported adverse events, manual therapy treatment description, patient health history, and patient satisfaction [22].

